### Intervention Group

The RA will meet each participant and conduct the pretest survey in the participant’s private hospital room. The computerized adaptive education intervention group will receive an advanced CKD education module with information about CKD risk factors, stages, treatment options, and lifestyle modifications. The RA will assist in advancing program modules but not offer any information or knowledge about CKD. The avatar will be an African American woman who will present statistics about African American individuals and CKD. The interactive component will allow participants to personalize the information received based on prior CKD knowledge, diabetes status, and the level of motivation. The interactive CKD video can be completed in 30-45 minutes. Following the patient’s completion of the advanced CKD education module, the RA will then readminister the General Health Knowledge and Intent survey.

The computerized adaptive education intervention group (and the usual health care control group) will complete the “What’s Next” form, to assess the patient’s commitment to specific self-care activities. Patients will select 3 health goals from a list of 10 options, rate their level of confidence in the ability to make change, and identify an action plan to accomplish each goal. Moreover, patients will be asked to report their needs from the medical care team and for community assistance, and they will be provided a resource list. The study will also ask if patients would like a primary care doctor and/or a nephrologist. This information will be relayed to the primary inpatient team. All the forms will be sent to the patient educator, a trained nephrology social worker.

We will encourage participants to complete the voluntary study in one visit. At 30 days after discharge, both groups will complete a follow-up call with the project RA. Participants will be queried about progress on goals set on the health commitment form, knowledge, and health intent.

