#### Secondary Outcomes

The secondary outcomes are patient motivation and intent. We will administer the CKD Self-Efficacy Scale [10], the Patient Activation Measure [11], and the Kidney Failure Treatment Preferences [12] before the intervention, immediately after the intervention, and at 30 days after discharge. We will administer the General Health Knowledge and Intent survey, an investigator-developed instrument, to assess RRT preferences and commitment to CKD self-care activities, including intent to seek a nephrologist, noncatheter dialysis access initiation, and completion of a transplant evaluation. Each patient will be contacted 30 days after discharge to discuss their commitment to each selected health goals, barriers, and treatment plan.

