### Statistical Methods

The planned total sample size is 170 (85 per group), which accounts for participant dropout due to unexpected discharges, changes in clinical status, or study disenrollment. The primary outcome will be measured by the change in baseline observed via the pretest, posttest, and follow-up surveys. Using a 2-sample, 2-tailed *t* test, a total of 154 (77 per group) participants is required to obtain >90% power to detect at least a 10% difference with the most conservative SD of 21% with a 1-sided type-1 error of 5%.

Our team will use the paired, 2-tailed *t* test with a Bonferroni adjustment for multiple comparisons with the usual hospital care and computerized adaptive education groups. We will use one-way ANOVA and chi-square tests to examine the significance between the usual hospital care and computerized adaptive education groups. This will determine whether there is a statistically significant difference between the two groups. We will also determine if the difference between observed and expected data is because of chance or a relationship between the usual health care and computerized adaptive education groups.

Data analysis will take place in an UCMC office. We will continue to monitor patient medical records after the study to determine whether they may be later included or excluded from the study.

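### Run as named, the tests leave patients missed at the 30-day call out of the 30-day comparison and ignore their posttest; a longitudinal model would use it, for a modest gain

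*Protocol article*

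**What the plan says.** The Primary Outcome and Statistical Methods sections define the primary outcome as change over the pretest, posttest and follow-up surveys. The secondary scales are given "before the intervention, immediately after the intervention, and at 30 days after discharge". The last of these contacts is by telephone: "At 30 days after discharge, both groups will complete a follow-up call with the project RA". The Intervention Group section adds that knowledge and intent are asked again at that call.

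The Methods paragraph of the Abstract assigns a Bonferroni-adjusted paired t test to the pretest, posttest and follow-up results. Statistical Methods repeats the paired t test and then states: "We will use one-way ANOVA and chi-square tests to examine the significance between the usual hospital care and computerized adaptive education groups". No other test is named for the analysis.

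On sample size, Statistical Methods says "a total of 154 (77 per group) participants is required to obtain >90% power". The inputs given there are a 10-point difference, an SD of 21 points and a 5% error taken on one side. Enrolment is raised to 170 to allow for losses, and the reasons listed are early discharge, clinical change and withdrawal. Failure to reach a patient at 30 days is not on that list, no 30-day loss rate is given, and the article does not say which time point carries the main comparison.

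**The concern.** A paired t test needs both surveys of the pair, and a one-way ANOVA needs the score being compared. A patient with a pretest and posttest but no 30-day score therefore drops out of the 30-day comparison. The posttest, which is likely to predict the missing score, contributes nothing to it. Using the pretest as a covariate does not change this, because a pretest-adjusted 30-day comparison still uses complete cases only.

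Some 30-day loss is plausible. The contact is a call after an acute admission, and the Discussion describes patients with urgent health concerns and poor access to outpatient care. The gift cards described under Ethical Considerations are tied to the pretest and posttest surveys. If the patients who are lost differ in their scores from those who are reached, the patients compared at 30 days may no longer be comparable between arms as randomised.

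**Working it through.** **Inputs from the protocol.** 85 randomised per arm; 77 per arm required; difference 10 points; SD 21; 5% error, 1-sided. The same sentence names a 2-tailed test, so both versions are shown.

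**Assumptions, not in the documents.** 30-day loss of 20, 30 or 40%. Correlations: pretest-posttest 0.6, pretest-30 days 0.5, posttest-30 days 0.5 or 0.7. The SD is 21 at each time.

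**1. The plan's own figure.** Power = Φ(10/SE − z), with SE = 21·√(2/n). For n = 77, SE = 3.384. With 1-sided 5% (z = 1.645) power is 90.5%, which reproduces the stated figure. With 2-sided 5% (z = 1.96) it is 84.0%. The built-in allowance for loss is 1 − 154/170 = 9.4%.

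**2. Three analyses of the 30-day difference, loss unrelated to scores.** Let n be the number per arm reached at 30 days.

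- Complete-case change score: variance = 2·21²·2(1 − 0.5)/n = 2·21²/n.
- Complete-case, pretest-adjusted: variance = 2·21²·(1 − 0.5²)/n = 661.5/n.
- Longitudinal model: variance = 661.5·[(1 − q)/n + q/85]. Here q is the squared partial correlation of posttest and 30-day score given the pretest: q = (r − 0.6·0.5)²/[(1 − 0.6²)(1 − 0.5²)]. For r = 0.7, q = 0.16/0.48 = 0.333. For r = 0.5, q = 0.04/0.48 = 0.083.

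Example with 30% loss (n = 59.5), r = 0.7, 2-sided. Pretest-adjusted: SE = √(661.5/59.5) = 3.334 and power = Φ(2.999 − 1.96) = 85.1%. Longitudinal: variance = 661.5·(0.6667/59.5 + 0.3333/85) = 10.01, SE = 3.163 and power = Φ(3.161 − 1.96) = 88.5%.

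Power, 2-sided 5%:

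| 30-day loss | Change score | Pretest-adjusted | Longitudinal, r = 0.5 | Longitudinal, r = 0.7 |
|---|---|---|---|---|
| 9.4% | 84.0% | 92.7% | 92.9% | 93.4% |
| 20% | 79.3% | 89.4% | 89.9% | 91.3% |
| 30% | 73.8% | 85.1% | 85.9% | 88.5% |
| 40% | 67.2% | 79.3% | 80.6% | 84.7% |

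The gain of the longitudinal model over pretest adjustment is 0.5 to 1.3 points at r = 0.5 and 1.9 to 5.4 points at r = 0.7, for 20-40% loss. A simulation of 3,000 trials per scenario at r = 0.7 gave 1 to 6 points. At 9.4% loss the gain is 0.2 to 0.7 points.

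With 1-sided 5%, the change-score comparison has 90.5, 87.1, 83.0 and 77.6% power at 9.4, 20, 30 and 40% loss. The gain beyond pretest adjustment at 20-40% loss is then 0.3 to 3.9 points.

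**3. Loss related to the posttest.** When response was simulated to rise with the posttest (log-odds 1 per SD, r = 0.7, 80/70/60% response), 2-sided power was 87/82/73% for the pretest-adjusted complete-case analysis and 91/88/83% for the longitudinal model. The bias of the pretest-adjusted estimate was −0.4 to −0.7 points.

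A second simulation compared unadjusted complete-case 30-day means (true difference 10, about 30% loss, r = 0.5 and 0.7):

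| How loss arises | Complete-case difference |
|---|---|
| Unrelated to scores | 10.0 |
| Low posttest scorers lost, same mechanism in both arms | 9.3 to 9.7 |
| Low posttest scorers lost, intervention arm only | 12.1 to 13.0 |

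An analysis using the posttest returned about 10.0 in every row. That follows from the set-up, because loss was made to depend only on the posttest.

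**The case against.** The strongest objection is that a condensed article may leave missing-data handling to an analysis plan that is not shown. The text does not say complete case, and imputation before a t test or ANOVA would be compatible with it. This stands to the extent that silence on missing data is not a fault here. What remains is that the article chooses its tests for the three-time-point scores, and those tests by themselves cannot use the posttest of a patient lost later.

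Two stronger readings are tempting, and the documents support neither. One is that the named tests bias the result. Bias needs loss related to scores, and nothing in the documents shows that. The 12.1 to 13.0 figures also require the mechanism to act in one arm only. The other is that a longitudinal model would lift 2-sided power from about 67% to about 85% at 40% loss. Most of that step (67.2% to 79.3%) comes from pretest adjustment, which is a separate choice; 5.4 points are left, and only at a correlation of 0.7.

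It is also fair to object that participants are encouraged to finish the study in one visit and that progress is counted by completed pretest and posttest, so the comparison between those two is essentially untouched. Finally, the longitudinal model still excludes patients who leave before any posttest. Both points stand.

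**Conclusion.** The point holds as a cheap improvement. As named, the 30-day comparison drops patients missed at the call and ignores their posttest. The cost is some precision, plus a risk of bias that is only partly avoidable. Beyond pretest adjustment, the recoverable power is about 0.5 to 6 points (2-sided) at an assumed 20-40% loss and a posttest-to-30-day correlation of 0.5-0.7, when loss is unrelated to scores. It is under 1 point at the 9.4% loss the plan allows for. If response depends on the posttest and the correlation is 0.7, the gain is about 4 to 10 points.

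The loss rates and correlations are all assumptions. A longitudinal model corrects only for loss explained by the observed pretest and posttest; loss through readmission or decline after discharge may not be explained by them.

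**What to change.** For the continuous scores (knowledge, self-efficacy, activation), replace the separate tests with one mixed model for repeated measures. Take the posttest and 30-day scores as outcomes, with arm by time, pretest by time and an unstructured covariance. Include every randomised patient with at least one post-baseline score, and report the arm difference at each time. Keep the complete-case comparison as a sensitivity analysis.

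The cost is wording in the analysis plan and one standard model; no new data or patients are needed. The Results section says data analysis has not occurred, so the change can still be prespecified. The model is slightly harder to explain than a t test, and it still rests on loss depending only on observed scores, which the report should state.

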### Participants and Eligibility

The study will take place at the University of Chicago Medical Center (UCMC). We will approach hospitalized, English-speaking, African American patients at UCMC, aged 18-70 years, who meet the criteria for advanced CKD (Stage 3b or greater) with an estimated glomerular filtration rate (eGFR) <45 mL/min/1.73 m^2^; they must not be on dialysis yet or have a history of kidney transplant. In order to be eligible, patients must have an eGFR <45 mL/min/1.73 m^2^ during the current hospitalization in addition to prior hospitalizations and/or outpatient visits. We will have access to prior UCMC inpatient and outpatient laboratory values. We will also have access to some inpatient and outpatient laboratory values from other medical centers through Epic Care Everywhere. The exclusion criteria include patients who are hospitalized in the intensive care unit, meet the Montreal Cognitive Assessment criterion for cognitive impairment, or require a proxy for study consent. We will enroll 170 participants and randomly assign 85 to the computerized adaptive education and 85 to usual hospital care.

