### Randomization

Participants will be randomly assigned using a computerized spreadsheet, assigning each participant a random number. Participants who are assigned an odd number will be assigned to the intervention group. Participants who are assigned an even number will be assigned to the control group. The RA will begin by identifying an eligible participant who consented to the Hospitalist Project. Then, they will use the randomization spreadsheet to determine if the participant will be part of the intervention group or the control group. They will then approach the patient with the appropriate form and study packet.

The RA will complete the randomization, assignment, and enrollment process.

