### Blinding

Trial participants will be blinded after group assignment. Participants will view the survey as a Google Form and will not be informed whether they are part of the intervention or control group. They will also receive a study packet, which will not identify if they are part of the intervention or control group. The research team will not be blinded.

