### Data Tracking

Data will be tracked in Google Sheets, linked to each survey. This will also help identify participant’s responses with the date, time, and enrollment number. Study packet responses will be saved in a password-protected box. Retrospective review will also be done to ensure each enrollment number matches the correct medical record number. Our research team will have access to the final trial dataset, and we will keep the data for 5 years after the study is completed.

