### Ethical Considerations

We obtained institutional review board (IRB) approval for this protocol (IRB 23-0385), and the parent study (the Hospitalist Project) is also IRB approved (IBR 16-1131). Written, informed consent to participate in the Hospitalist Project will be obtained from all participants. Participants will also verbally consent and be enrolled in the I-C-CKD study.

Patients will be informed that the study is completely voluntary and may withdraw at any time. Discontinuation will also occur if patients are in acute distress or experience declining health conditions during hospitalization. For example, if the patient is transferred to intensive care unit, is intubated, or has an altered mental status and can no longer participate, then we will withdraw them from the study. Patients will also be able to meet with patient educator who is a licensed clinical social worker if they are interested in additional information, are under distress, or want posttrial care.

Patients will receive US $25 gift cards upon completion of the pretest and posttest surveys and US $10 for partially completed surveys. All participants will be compensated. This study is minimal risk, as an education intervention is the only experimental procedure involved. Additionally, reports will be made to the IRB in the case of an adverse event, along with any protocol modifications to the investigators, IRB, trial participants, journals, and regulators.

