## Results

Recruitment for the I-C-CKD study began May 2, 2023. We are currently recruiting and have enrolled 96 patients who completed both pretest and posttest surveys as of December 2024. This includes 50 patients in the control group and 46 patients in the intervention group. Data analysis has not occurred. We will communicate trial results to trial participants, health care professionals, and the public via a journal publication.

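### Post-study record review by an unblinded team may change who is in the trial, so the analysed groups need not be the randomised groups

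*Protocol article*

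**What the plan says.** The last paragraph of Statistical Methods in the protocol article contains the rule: "We will continue to monitor patient medical records after the study to determine whether they may be later included or excluded from the study". Nothing around it says what finding in the record would lead to inclusion or exclusion, what dates the review covers, when it closes, or who decides.

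Other sections bear on how that rule would operate:

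- Blinding: "The research team will not be blinded".
- Randomization: "The RA will complete the randomization, assignment, and enrollment process". The Intervention Group and Control Group sections have the same research assistant (RA) give the surveys.
- Data Tracking: "Our research team will have access to the final trial dataset".
- Participants and Eligibility: the eGFR criterion must be met "during the current hospitalization in addition to prior hospitalizations and/or outpatient visits". Outside laboratory values are only partly available.
- Ethical Considerations: a patient who deteriorates and "can no longer participate, then we will withdraw them from the study".
- Results: the investigators "have enrolled 96 patients who completed both pretest and posttest surveys", 50 control and 46 intervention, and analysis has not yet been done.

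The article nowhere says that participants are analysed in the group to which they were randomised.

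**The concern.** Randomisation protects the comparison only while membership of the two groups is fixed by the allocation. The quoted sentence makes membership depend on information that arrives after the study, when survey results exist, and leaves the decision with people who know each patient's group. It works in both directions, since patients may be added as well as removed, so it is wider than ordinary dropout.

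If the reason for removal is related to how much a patient's knowledge changed, and is applied differently in the two groups, the estimated difference shifts and the type I error is no longer the stated one. This is not a detail left to an unseen analysis plan. It is a stated rule, and following it as written can bias the primary comparison.

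**Working it through.** **Reproducing the plan's figure.** Inputs from Statistical Methods: difference 10, SD 21, one-sided 5%, power above 90%. Normal approximation: n = 2 × (1.645 + 1.282)² × 21² / 10² = 75.6, so 76 per group. The t-test version gives 76.2, so 77, with power 90.3% at 77. The stated 77 per group is reproduced. At two-sided 5% the t-test needs 94 per group, and 77 would give 83.5%. The sample-size sentence names both a 2-tailed test and a 1-sided error, so both one-sided 2.5% and one-sided 5% are shown below.

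**How many removals to consider.** The documents give no exclusion rate, so this is an assumption. The plan's own dropout allowance is 85 − 77 = 8 per group (1 − 154/170 = 9.4%). I use 4 and 8, all from the intervention group.

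**Expected shift.** Assume no true effect, 85 per group and normally distributed change with SD 21. If exactly the k lowest changers are removed, the remaining mean rises by k × |m| / (85 − k) × 21, where m is the mean of the k lowest of 85 standard normal values (−2.03 for k = 4, −1.75 for k = 8).

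- k = 4: 4 × 2.03 / 81 × 21 = 2.1 points.
- k = 8: 8 × 1.75 / 77 × 21 = 3.8 points.

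If removal follows a criterion correlated ρ with change, the shift is ρ times this. At ρ = 0.3 it is 0.3 × 2.1 = 0.6 and 0.3 × 3.8 = 1.1 points. At ρ = 0 it is nil.

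**False-positive rate favouring the intervention** (two-sample t test, 100,000 simulated trials per row):

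| Link between removal and change | Removed | Shift (points) | Nominal 2.5% | Nominal 5% |
|---|---|---|---|---|
| None (ρ = 0) | 4 | 0 | 2.6% | 5.0% |
| None (ρ = 0) | 8 | 0 | 2.4% | 4.8% |
| ρ = 0.3 | 4 | 0.6 | 4.0% | 7.5% |
| ρ = 0.3 | 8 | 1.1 | 5.4% | 9.9% |
| Exactly the lowest changers | 4 | 2.1 | 10.6% | 17.3% |
| Exactly the lowest changers | 8 | 3.8 | 24.3% | 34.7% |

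The first two rows differ from nominal only by simulation error. The last two are an extreme case, but not a strict upper bound: removing 4 low changers from intervention and 4 high changers from control shifts the difference by 2 × 2.1 = 4.2 points.

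**The case against.** The best defence is that the sentence means only late verification of eligibility. The eGFR criterion relies on earlier visits, some at other centres whose records are incomplete, so a pre-randomisation value might surface later. Exclusion for such a fact, judged without knowledge of group or outcome, would do little harm. That reading is plausible, but the text does not confine the review to it, and confirming facts that already existed does not require open-ended monitoring after the study.

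Several stronger readings are tempting, and the documents do not support them:

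- **That patients will be removed for later kidney course or dialysis start.** No section says so.
- **That the withdrawal rule in Ethical Considerations also defines the analysis set.** It ends participation for patients who cannot continue. It does not say that collected data are discarded, and the sample size already allows for such dropout.
- **That only completers will be analysed.** The line in Results reports recruitment status. It leaves the randomised numbers by group unseen but sets no analysis rule.
- **That losses are likely to be greater in the intervention group because its module is longer.** The module takes 30 to 45 minutes, but the Control Group section also mentions a video module for controls, although elsewhere only printed materials are described. The 50 to 46 split is compatible with equal allocation (exact binomial p = 0.76). Without denominators, this neither shows nor excludes differential loss.

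The absence of an intention-to-treat statement from a condensed article is not a fault in itself. The fault lies in the sentence that is there.

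**Conclusion.** The point holds for one sentence: an open-ended inclusion and exclusion rule, applied after the study by a team that is not blinded. A reader might infer that the result will be biased, or biased towards the intervention. The documents show neither.

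The possible size depends wholly on assumed inputs: the number removed, from which group, and how closely the reason tracks knowledge change. With 4 to 8 intervention patients removed, the effect runs from nothing, through a shift of about 0.6 to 1.1 points at a correlation of 0.3, to 2.1 to 3.8 points if the lowest changers are singled out. These compare with a target difference of 10 points. The moderate case roughly doubles the error rate at most, and the extreme case would need near-deliberate selection.

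The severity is should-fix: the defect touches the primary comparison and is cheap to remove, but harm is conditional.

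**What to change.** Replace the sentence in Statistical Methods with:

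> The primary analysis includes all consented, randomised participants in their assigned group, using all data collected. No one is added after the study. A participant may be excluded later only for an eligibility failure shown by data dated before randomisation, judged without knowledge of group or survey results and before the analysis; a sensitivity analysis retains them.

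Alongside it:

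- Apply the same rule to participants already enrolled, whose eligibility can no longer be settled before randomisation.
- Reconcile Trial Design, where consent comes before assignment, with Randomization, where the RA looks up the group and then approaches the patient. Report by group those assigned who declined. Until this is settled, a population of all randomised patients could include people who never consented.
- Clarify in Ethical Considerations that withdrawal ends participation but that data already collected are kept unless consent is withdrawn.
- Report the numbers randomised by group beside the completers given in Results.

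The cost is mainly wording, plus notice of the modification to the institutional review board and someone masked to group and survey results to judge late eligibility questions. A few ineligible patients may remain and dilute the effect slightly. Because no analysis has been done, the change can still be made credibly.
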